### Recruitment {15}

Potential participants will be identified through specialist neurology clinics at the trial centre or referred to the trial team from other MS/neuroscience centres and hospitals. Candidate participants will then be seen in clinic or contacted via telephone/video call to discuss the trial directly with a member of the trial team and ‘prescreen’ to ensure that the interested participant is likely to fulfil the general criteria to enter the trial and be able to comply with the trial assessments and interventions. The potential participant will be given a copy of the participant information sheet (PIS) and ICF and asked to contact the trial team at an interval of no less than 24 h to confirm if they would like to proceed to screening.

## Assignment of interventions: allocation

### Sequence generation {16a}

Eligible participants will be randomly assigned to metformin + clemastine (active arm) or placebo (control arm) in a 1:1 ratio using a minimisation with random element method. The stratification factors used in the randomisation will be: age (≤ 40 vs > 40 years), baseline MS DMT treatment category (1 vs 2) [5], sex (male vs female), and disability (an EDSS step ≤ 4.0 vs > 4.0).

### Concealment mechanism {16b}

A web-based central randomisation system (Sealed Envelope) will allocate the participant a treatment code that will relate uniquely to a supply of IMP.

### Implementation {16c}

Access to the web-based randomisation system will be via individual user accounts provided to the CI and suitably trained and delegated members of the research team. Immediate allocation of treatment will be performed by the Sealed Envelope system following enrolment by the site investigators, with documentation of the decision sent in a confirmatory email.

## Assignment of interventions: blinding

### Who will be blinded {17a}

Throughout the trial, investigators and participants will be blinded to the treatment allocation. The blind will be protected by means of: identical appearance of tablets for active and placebo drugs, equal numbers of tablets prescribed to participants in each arm, coded drug supplies being provided to the clinical trials pharmacy, and the randomisation list being held securely from the investigator’s team (with provision for unblinding in emergencies if required). Staff in the pharmacy and the trial coordinator will be unblinded to trial treatment and allocation. An additional layer of blinding is added by the anonymisation of VEPs and MRIs, such that they are analysed without reference to any participant information.

### Procedure for unblinding if needed {17b}

The online randomisation system will be used for emergency unblinding. To maintain the overall quality and legitimacy of the clinical trial, treatment code breaks may occur only in exceptional circumstances when knowledge of the actual treatment is essential for further management of the participant. If the investigator or treating healthcare professional believes unblinding is necessary, the investigator will be able to break the treatment code using the randomisation system. Appropriately trained and delegated site staff will be given the necessary access rights and permissions to access this facility. The name, contact details of the unblinder, and reason for unblinding will be recorded within the randomisation system.

## Data collection and management

### Plans for assessment and collection of outcomes {18a}

#### Visual evoked potentials

VEPs will be assessed by means of a Vision-Search Plus system (VisionSearch, Sydney, NSW, Australia). The stimulus protocol for full-field VEP (primary outcome) has been selected to comply with guidelines from the International Society for Clinical Electrophysiology of Vision [67]. The visual stimulus will be generated on a high-resolution liquid crystal display, with a 2 Hz reversing check pattern of size of 60 min of arc. The participant will be seated 50 cm from the screen. All will be optimally refracted for near vision, and pupil dilatation will not be required. Electrical signals will be recorded from a channel formed between gold-cup electrodes (Grass Technologies, West Warwick, RI, USA) positioned frontally in the midline and 2.5 cm above the inion (Fz-Oz); a ground electrode will be placed on the ear lobe, and conductive gel (0.5 ml) injected under each. Between 3 and 5 averaged recordings will be taken per eye, and the weighted average of these used to measure the N75, P100 and N145 latencies and the amplitude between the N75 and P100. Two blinded raters will be responsible for ensuring quality control of each VEP record and for latency and amplitude determination.

For the multifocal VEP (secondary electrophysiology outcome), we will use the aforementioned equipment, this time to monocularly present a stimulus consisting of 56 cortically scaled segments, each containing a 4 × 4 checkerboard reversing in a pseudorandom sequence. Four gold-cup electrodes (Grass Technologies) will be used for bipolar recording: a vertical channel (using electrodes placed in the midline 2.5 cm above and 4.5 cm below the inion) and a horizontal channel (via electrodes placed 4 cm either side of the inion). The resultant VEP signals from each of the 56 segments are amplified 100,000 times and band-pass filtered (1–20 Hz). Amplitude is defined as the largest peak-trough signal from either the vertical or horizontal channel, within an interval of 70–200 ms, while latency is taken as the second peak of this maximum amplitude wave. Segments with no detectable amplitude are assigned an amplitude of 0 nV but are not assigned a latency. The software then averages the amplitudes from each segment and averages the latencies from only those segments with recordable signal. In order to be included in the analysis, the baseline recording must have recordable signal in at least 28 of the 56 segments, and a prolonged baseline latency is defined as being ≥ 151 ms. Progression analysis will then be performed across each of the 56 segments from each of the trial visits by two blinded raters, to determine the change in multifocal-VEP latency and amplitude for each affected eye.

#### MRI

MRI scans will be performed at baseline and at 26 weeks, using a Siemens 3 T Prismafit scanner (Siemens, Erlangen, Germany) with 20-channel head-neck coils. Each scan will include three-dimensional (3D) magnetisation transfer imaging (for the calculation of MTR maps), 3D T1-weighted imaging (for volumetric measures and tissue segmentation), interleaved 2D proton density-weighted and T2-weighted scans (for lesion identification), 3D fluid-attenuated inversion recovery (for lesion identification and contouring of T2 hyperintense lesions) and 3D macromolecular tissue volume imaging (MTV). Sequences sensitive to grey matter lesions will also be collected (double inversion recovery (DIR)) [68, 69]. The 3D images will be registered to halfway space. A baseline lesion mask will be generated automatically from the fluid-attenuated inversion recovery, edited, then propagated to the follow-up and updated with any new or enlarging lesions. New and enlarging lesion identification, contouring of grey matter lesions, and checking will be done by three different masked observers.

#### Optical coherence tomography

Heidelberg Spectralis spectral domain OCT (Heidelberg Engineering, Heidelberg, Germany) with eye tracking function (TruTrack, Heidelberg Engineering) will be used to obtain quantitative retinal thickness data and morphological cross-sectional information. The same Spectralis machine will be used for participant scanning throughout the trial, with scans obtained by experienced OCT operators. Scans of the peripapillary RNFL will be obtained by recording a high-resolution ring scan (diameter 12°) around the disc (ART 100). Macular volumetric scans will be obtained using the standard posterior pole protocol of the Spectralis OCT, comprising 61 single lines of 15 frames (30° × 25° volume scan centred on the fovea) obtained in high-speed mode with ART 16.

The quality of ring and volume scans will be assessed using OSCAR-IB consensus criteria for retinal OCT quality assessment [70]. Two independent and blinded raters will determine macular and RNFL thicknesses on coded scans for each participant.

#### Visual fields

A Humphrey Field Analyser (Carl Zeiss Meditec, Jena, Germany) will be used to conduct visual field testing of each eye at baseline and week 28, deploying the Swedish interactive threshold algorithm (SITA) standard strategy (30-2 protocol). Reliability criteria will be fixation losses of 20% or less, false-positive results of 15% or less, and false-negative results of 33% or less.

#### Visual acuity

Examination of high and low-contrast letter acuity will be performed for each eye separately at baseline, week 12, and week 28, with refractive correction for distance. High contrast letter acuity testing will be completed using Early Treatment Diabetic Retinopathy Study (ETDRS) visual acuity charts on a large ETDRS illuminator cabinet (Precision Vision, Woodstock, IL, USA). Low-contrast letter acuity testing will be completed using retroilluminated 2.5% and 1.25% Sloan Revised low contrast charts (Precision Vision, Woodstock, IL, USA). Each testing round will begin at 4 m. For each test (ETDRS acuity, low-contrast letter acuity 2.5% and 1.25%), the total number of letters correct will be recorded.

#### Eye tracking

A portable infra-red saccadometer (Ober consulting) will be fitted to the participant, which automatically presents a stimulus protocol and records the reaction times. Three sequences of stimuli (the step, antisaccade and Wheeless tasks) will be collected [71]. An additional substudy of participants (outside of the trial protocol), using an Eyelink 1000, will undertake the prosaccade and double-step tasks from the DEMoNS protocol [72]. These will be performed at screening visit 2 and week 28. These exploratory endpoints will be reported outside of the main trial manuscript.

### EDSS

All participants will have their disability evaluated by the EDSS, by a neurostatus-certified member of staff (doctor, specialist nurse or physiotherapist).

### Plans to promote participant retention and complete follow-up {18b}

As a research team, we will do our best to support participants’ retention in the trial. If treatment withdrawal of both IMPs occurs at any time point after randomisation, the participant will be asked if they would agree to continue with the trial assessments (both safety and efficacy). If withdrawal occurs within 2 months of starting IMP (whether or not the participant has taken any IMP during this time), the CI has the option of replacing that individual.

### Data management {19}

CCMR Two will use standardised procedures for data entry, coding, security, storage, and analysis to ensure data quality and confidentiality, as set out in the trial’s Data Management Plan v4.0. Source data will be recorded and subsequently entered electronically into MACRO, a secure and validated trial database which includes closed response entries and range restrictions to maximise valid data entry. This will be done contemporaneously, typically within 7 working days of completion of source documentation. Critical data points will undergo double data entry by different team members. Each participant will be assigned a unique trial ID to de-identify data. The trial coordinator and trial monitor will undertake quality control checks on data and issue queries in line with the trial-specific monitoring plan. Upon completion of the trial, the dataset will be locked, and analyses will be performed by the trial’s statistician. Regular audits of data quality and completeness will be conducted.

### Confidentiality {27}

All investigators and trial site staff involved in CCMR Two will comply with the requirements of the General Data Protection Regulation (GDPR) 2018, Data Protection Act 2018 and Trust policy with regards to the collection, storage, processing, transfer and disclosure of personal information and will uphold the act’s core principles. The trial staff will ensure that the participants’ anonymity is maintained. The participants will be identified only by initials, date of birth and a participant ID number on the case report form and any electronic database. All documents and data will be stored securely and only accessible by trial staff and authorised personnel. Access to this data will be restricted to authorised members of the trial team via a two-factor authentication system.

### Plans for collection, laboratory evaluation and storage of biological specimens for genetic or molecular analysis in this trial/future use {33}

Blood tests performed for this trial are as follows: full blood count (FBC), liver function tests (LFTs), urea and electrolytes (U&Es), C-reactive protein (CRP), and serum glucose. Vitamin B12 will be tested at the screening 2 visit. For female participants of childbearing potential, a serum pregnancy test will also be performed at the screening 2 visit. In addition to these tests, blood samples will be collected, processed and stored in − 80 °C freezers in the Clifford Allbutt Building for future analysis, if the participant has consented to this optional research sample collection. Samples will be labelled with trial-specific identifiers. Samples of blood, the components of blood (i.e. plasma/serum/cells), and stool samples may be shared with other collaborating academics or with industrial third parties (maybe both within and outside the UK and EEA where data protection laws are less strict) that are under contract to carry out sample analysis. Samples will only ever be used for research that is approved and deemed appropriate by an ethics committee. If there are unused samples left at the end of the trial, we will ask for ethical approval to use these in another project.

## Statistical methods

### Statistical methods for primary and secondary outcomes {20a}

A detailed statistical analysis plan (SAP version 1.0 (14 January 2025)) provides an account of the statistical methods for analysing the trial. Primary efficacy analyses will be based on the modified intent-to-treat (mITT) population with supplementary analyses with the PP population (definitions Sect. 20c).

### Primary outcome measure: full-field VEP

The primary analysis of this trial will compare the mean change in the P100 latency of the full-field VEP from baseline and week 26, between metformin + clemastine (research arm) and placebo (control arm). This will be based on eligible eyes with delayed (≥ 118 ms) baseline P100 latency. Eligible eyes will additionally have RNFL thickness ≥ 70 μm (see outcomes Sect. 12 for the definition of eligible eyes). A mixed-effect model will be used for eyes nested within participants, with random effects for participants and fixed effects for treatment allocation at randomisation, baseline P100 latency and stratification factors.

Fixed effects: treatment allocation, baseline P100 latency, age at consent (≤ 40 years vs > 40 years), sex (male vs female), baseline MS DMT treatment category (1 vs 2) [5], screening EDSS (≤ 4.0 vs > 4.0).

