### Participant timeline {13}

The screening visit will be divided into two sets of assessments. On the first, after signing of the informed consent form (ICF), the trial team will review the participant’s medical history, imaging and records to confirm the diagnosis of RRMS [32] and their eligibility for inclusion (Table 1). Participants will then have their screening VEP assessments to ensure there is detectable demyelination in the visual pathway. Our data suggest that in the region of 25–50% of potential participants will not pass screening at this point; in the ReBUILD trial, it is noteworthy that 75 failed screening on this same criterion to yield 50 eligible participants [23]. If these assessments are satisfied, the individual would then be invited to return for a second series of screening investigations including blood tests, EDSS assessment, and OCT to ensure the criteria outlined in Table 1 are similarly met; a much lower attrition rate is anticipated at this point.

Following documented permission from the potential participant when signing the ICF, their usual treating neurologist and/or general practitioner (GP) will be contacted to detail their involvement in the trial; if they are not able to be randomised after attending screening, reasons for this will be communicated to both the participant and referring clinician. We will also maintain a log of all who are ineligible for the trial and all eligible participants that will not be randomised because they declined participation. This process will enable generalisation of the trial results in accordance with the Consolidated Standards of Reporting Trials (CONSORT) guidelines of 2010 [66].

Baseline assessments will take place after randomisation and up to 2 weeks prior to commencement of IMP. After the baseline visit, the MRI will be reviewed for quality control. If this passes, the participant will start IMP within 2 weeks as outlined. In the unlikely event of the MRI not passing quality control, it is possible that we would require a repeat MRI scan. This would be scheduled at least 2 days prior to the commencement of IMP.

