Participants receive 24 weeks of treatment. Participants are to be seen at Addenbrooke’s hospital after 4 weeks, 12 weeks, 26 weeks, and a final visit at 28 weeks from treatment initiation. A visit window for week 4 and week 12 visits of ± 7 days will be permitted where scheduling participant visits is difficult or in the event of ill health or transport issues. A visit window of + 7 days will be permitted for the week 26 visit if a similar problem arises. A visit window of ± 14 days will be permitted for the week 28 visit.

A summary of participant assessments is presented in Table 2.

**Table 2 Tab2:** Schedule of assessments for CCMR Two

**Assessment**	**Screening 1**	**Screening 2**	**Baseline**	**Treatment phase**						Week 26	Week 28
**Clinic visit number**	**1**	**2**	**3**	No visit	No visit	**4**	**5**	No visit	No visit	**6**	**7**
**Visit window**	**Day − 70 to − 14**	**Day − 70 to − 14**	**Day − 14 to − 7**	Day 1	Day 15	**Week 4 (± 7 days)**	**Week 12** **(± 7 days)**	Week 24	Week 24	**Week 26 (+ 7 days)**	**Week 28 (± 14 days)**
Informed consent	X			**Start IMP**				**Stop IMP**			
Eligibility assessments	X	X									
Medical and MS history	X										
Physical examination^1^		X								X	
EDSS assessment		X								X	
Concomitant medication check	X		X			X	X			X	
Randomisation		X^2^									
Adverse event assessments		X	X			X	X			X	X
IMP dispensing			X			X	X				
IMP dose increase					X	X					
IMP compliance check						X	X			X	
Safety bloods		X				X	X			X	
Optional research bloods (for storing serum, plasma and whole blood)		X					X			X	
Optional stool sample			X			X			X		
12 lead ECG		X									
Pregnancy test (women of childbearing potential only)		X	X			X	X			X	
Full-field VEP	X		X				X			X	
Multifocal VEP	X		X				X			X	
OCT		X									X
Visual fields			X								X
Visual acuity			X				X				X
Eye tracking		X									X
MRI imaging			X							X^3^	

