### Sample size {14}

The primary endpoint is the change in the P100 latency of the VEP between baseline and week 26 for each eligible eye. An average reduction of 3.0 ms/eye in VEP at week 26 between metformin + clemastine (research arm) and placebo (control arm) will be an important treatment effect to detect. There is no evidence for an interaction of VEP between eyes. With a 5% significance level (two-sided), 80% power, and a common standard deviation of 5 ms, 45 eyes in each arm are required to detect a difference of 3.0 ms/eye in the mean change of VEP at week 26 from baseline between the two treatment groups (nQuery). The common standard deviation of 5 ms was based on the ReBUILD study [23], which was approximately 4.1 ms, and added around 20% (4.1 × 1.20 = 4.92) more variation. Allowing for 10% non-compliance, that is 50 eyes per arm: it was originally planned to recruit 50 participants. Following the planned interim analysis meeting held on 28/06/23, the trial sample size increased to 70 participants as around 50% of participants had only one eligible eye at screening. The Independent Data Monitoring Committee (IDMC) supported the plan to increase recruitment to reach the required eligible eyes.

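### The primary model adjusts for one of two scheduled pre-treatment P100 latencies; adding the screening value would gain some precision from data already collected

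*Protocol article*

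**What the plan says.** The article's section on the primary outcome analysis describes a mixed model for eyes nested within participants, with "fixed effects for treatment allocation at randomisation, baseline P100 latency and stratification factors". It then lists the fixed effects: treatment, baseline P100, age group, sex, DMT category and EDSS group. Baseline P100 is the only latency among them. The outcome is change in P100 from baseline to week 26 in each eligible eye.

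A second pre-treatment latency exists. Section {13} says: "Participants will then have their screening VEP assessments to ensure there is detectable demyelination in the visual pathway". In Table 2 the row "Full-field VEP" is marked at screening 1, baseline, week 12 and week 26. The multifocal VEP row is marked at the same visits, and the multifocal analysis reuses the primary model. Baseline assessments come after randomisation but before the first dose, so both early readings precede treatment.

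The sample size section {14} states: "With a 5% significance level (two-sided), 80% power, and a common standard deviation of 5 ms, 45 eyes in each arm are required", in order to "detect a difference of 3.0 ms/eye in the mean change of VEP at week 26 from baseline between the two treatment groups".

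**The concern.** A single baseline reading carries its own visit-to-visit error. That error enters the change score directly, and adjusting for the same reading removes only part of it. A second pre-treatment reading of the same eye gives a better estimate of where the eye started. Patients must be on stable DMT with no optic neuritis in the qualifying eye for two years. By the visit windows the two readings are at most 63 days apart (day -70 to day -7). Little true change is expected in that time, so the screening value should be informative.

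What is at stake is precision on the primary endpoint. Recruitment closed in October 2024, so the analysis is the main place where precision can still be gained. Validity is not at stake.

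**Working it through.** **1. The plan's own figure.** Inputs from section {14}: difference 3.0 ms, SD of change 5 ms, two-sided 5%, 80% power. The SD comes from an earlier clemastine trial, "which was approximately 4.1 ms, and added around 20% (4.1 × 1.20 = 4.92) more variation".
- Normal approximation: n = 2 × (1.960 + 0.842)² × 5² / 3² = 43.6, so 44 per arm.
- Two-sample t-test (noncentral t): 44 per arm gives 79.5% and 45 gives 80.4%, so 45 per arm.
- 45 / 0.9 = 50, matching "Allowing for 10% non-compliance, that is 50 eyes per arm".

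The stated figure reproduces. It takes no credit for covariate adjustment.

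**2. Gain under equal correlation.** Let r be the correlation between any two visits (not in the documents). The residual variance of week-26 latency, as a share of its total variance, is 1 - r² given one earlier reading and 1 - 2r²/(1 + r) given two. The ratio is (1 + 2r)/(1 + r)². The power column treats 5 ms as the residual SD under the planned model and the 45 eyes per arm as independent, as section {14} does.

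| r | variance ratio | fall | SD (ms) | power, 45 per arm | eyes per arm for 80% |
|---|---|---|---|---|---|
| 0.5 | 2.0/2.25 = 0.889 | 11% | 4.71 | 84.7% | 40 |
| 0.7 | 2.4/2.89 = 0.830 | 17% | 4.56 | 87.1% | 38 |
| 0.9 | 2.8/3.61 = 0.776 | 22% | 4.40 | 89.2% | 35 |

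**3. Gain by share of measurement error.** Write the change variance as 25 = 2e + c, where e is the error variance at one visit and c is the variance of true change. Let T² be the true between-eye variance (T = 8 or 12 ms, assumed). With outcome week 26 minus baseline, the residual variances are:
- baseline only: e + c + T²e/(T² + e)
- baseline and screening as separate covariates: e + c + T²(e/2)/(T² + e/2)
- screening/baseline mean in place of baseline: 2e + c - (e/2)²/(T² + e/2)

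Worked case, T = 8 and all change variance error (e = 12.5, c = 0):
- baseline only: 12.5 + 64 × 12.5/76.5 = 22.96
- both: 12.5 + 64 × 6.25/70.25 = 18.19, ratio 0.79
- mean: 25 - 39.06/70.25 = 24.44, ratio 1.065

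| error share of change variance | both covariates, T = 8 / 12 | mean as covariate, T = 8 / 12 |
|---|---|---|
| 25% | -5.9% / -6.1% | +0.4% / +0.2% |
| 50% | -11.1% / -11.8% | +1.7% / +0.8% |
| 75% | -16.0% / -17.4% | +3.7% / +1.7% |
| 100% | -20.8% / -23.0% | +6.5% / +3.1% |

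The mean option loses because the error in the single baseline stays in the outcome and is adjusted for less well.

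**4. Selection at 118 ms.** Step 3 ignores eligibility. Simulation with selection at 118 ms at both visits gave a fall of 21% when all change variance is noise and 4% when three quarters of it is true change. Power at 45 per arm was 88.7% and 82.0% respectively. If all change variance were true change, the gain would be zero.

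**5. Mixed model.** Section {14} says "the trial sample size increased to 70 participants as around 50% of participants had only one eligible eye at screening". That implies about 35 × 1 + 35 × 2 = 105 eyes. The simulation used 150 runs per setting, an assumed within-participant correlation of 0.3 and no stratification factors. The mean standard error of the treatment effect went from 1.00 to 0.91 (all noise), from 1.05 to 1.00 (half noise), and stayed at 1.05 (5% noise). No bias was visible. Type I error was near 5%, though 150 runs fix that only to a standard error of √(0.05 × 0.95/150) = 1.8 percentage points.

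**The case against.** The strongest reply is that nothing here is wrong: a mixed model adjusted for a single baseline is standard and valid, and the power statement does not depend on a second covariate. That stands. This is a missed efficiency.

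The second reply is that the size of the gain is unknown. That also stands. No section gives test-retest error or a between-visit correlation. The data collection section already has 3 to 5 recordings averaged per eye and two blinded raters, which reduces noise within a session but not between visits. Screening may precede baseline by several weeks, so the two readings need not be close replicates.

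A reader might infer that measurement error must dominate because the 3 ms target is smaller than the 5 ms SD. It does not follow: effect size relative to SD says nothing about how change variance divides between error and true change. A reader might also infer that the trial is underpowered as stated; this point does not show that, since 45 eyes per arm reproduces. Selection at screening might be thought to bias the comparison, but the screening value precedes randomisation, so selection only shrinks the gain somewhat.

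The last reply is timing. SAP 1.0 is dated January 2025 and analysis was due to start in April 2025, so a change to the primary covariates is not costless.

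**Conclusion.** The point holds as an optional improvement in precision. Two pre-treatment latencies are scheduled for every randomised participant, and the covariate list in the article uses one. Using both as separate covariates leaves outcome and estimand unchanged and lowers residual variance whenever there is some visit-to-visit error.

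The working range is a fall of about 4% to 22%, or power at 45 eyes per arm of about 82-89% against 80.4%. The unselected closed form reaches 23% in its most extreme cell, and selection at 118 ms reduces that. The range rests on assumed between-visit correlations of 0.5 to 0.9, or on measurement error making up 25% to 100% of change variance. Below that the gain fades: at a 5% error share the simulated standard error did not move.

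**What to change.** In the primary model, add the same eye's screening P100 latency as a second fixed-effect covariate beside baseline P100. In the multifocal model, add the screening multifocal latency in the same way. Keep the outcome as change from baseline to week 26, and keep eye eligibility as defined.

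Do not replace the baseline covariate with the screening/baseline mean while the outcome is change from the single baseline. The mean helps only if change is also taken from the mean, or if week-26 latency is the outcome.

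The cost is one degree of freedom per model, no new data, and a documented SAP amendment before unblinding. The amendment should say what happens to an eye without a usable screening latency, which should be rare because screening decides eligibility. If unblinding has already taken place, keep the single-baseline model as primary and report the two-covariate model as a labelled sensitivity analysis.
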